Although the treatment with artesunate compared to quinine considerably reduces mortality in severe and cerebral malaria, the case fatality rate remains high at between 20% and 30%[[1]](#endnote-2). Improved supportive care can importantly further reduce mortality; a series from a well equipped intensive care unit in Paris showed a mortality of 11% in patients with severe malaria[[2]](#endnote-3). Supportive treatments include highly technical aids like renal replacement therapy and mechanical ventilation, but also easier to achieve treatments like enteral feeding. In the well equipped intensive care setting early start of enteral feeding in a wide variety of patients, including those with sepsis, is now common practice. Nutrition supplies vital cell substrates, antioxidants, vitamins, and minerals, essential for normal cell function. Studies have shown that early enteral feeding preserves the barrier function of the gut, has positive effects on immune functions, is associated with a decrease in hypermetabolism and organ failure, and reduces the chance of bacteraemia [[3]](#endnote-4) [[4]](#endnote-5) [[5]](#endnote-6) [[6]](#endnote-7) [[7]](#endnote-8) [[8]](#endnote-9). In severe malaria, patients are often poorly nourished and hypoglycaemia is a common complication, especially in patients receiving quinine. Also, bacteraemia with Salmonella species is more common in severe malaria[[9]](#endnote-10), associated with increased bacterial translocation in the gut. Enteral feeding might have a beneficial effect here. The downside of starting enteral feeding in the dependent comatose patient is the risk of aspiration pneumonia; this risk is also present in the mechanically ventilated patient[[10]](#endnote-11) [[11]](#endnote-12), although the risk is lower with the use of post-pyloric enteral feeding tubes[[12]](#endnote-13) [[13]](#endnote-14) [[14]](#endnote-15). A supine position of the patient is a risk factor[[15]](#endnote-16). Routine endotracheal intubation to protect the airway in comatose malaria patients is not a feasible option in most of the tropical countries where malaria is endemic. The use of enteral feeding through a naso-gastric (NG) tube might thus induce a much higher risk of aspiration pneumonia, outweighing the theoretical benefits.

At Chittagong Medical College Hospital (CMCH), the current practice is to start early enteral feeding through a NG-tube, with a volume of 2-4ml/kg per feed every 2 hours, avoiding 2 late night feeds, resulting in a total of 10 feeds per day for adults. For children fluid supplementation is as follows: for age 2-4years: 100 - 120ml/kg/day; 4-8yrs 90-100ml/kg/day; 8-12yrs 70-90 ≥12 yrs 60-70ml/kg/day given every 2 hours round-the-clock. In both the cases the enetral feeding volume is derived from total volume subtracting the volume given as i.v. fluids. The feeds are prepared from locally available food by blending or commercially available powder form. Although not formally assessed, aspiration pneumonia is a rather common complication of NG feeding in CMCH. Factors that can contribute include the supine position of the patient and no check for gastric retention before the next feeding. We here propose a randomized trial to compare the start of early versus late nasogastric tube feeding, with aspiration pneumonia, incidence of hypoglycaemia and coma recovery times as primary outcome measures.

Materials and Methods

*Place and Period of Study*

It is planned to study 124 consecutive patients, age 2 y/o, with cerebral *Plasmodium falciparum* malaria, defined as a Glasgow Coma Score (GCS) below 11or BCS <3 (for pre-verbal children) and the presence of asexual stage *P. falciparum* parasites in a peripheral blood slide, admitted to Chittagong Medical College Hospital, Chittagong, Bangladesh. Patients will be recruited from the internal medicine wards (ward 13, 14, and 16) and from the paediatric ward.

*Inclusion Criteria*

1. Cerebral falciparum malaria defined as a GCS<11or BCS <3 (for pre-verbal children), and the presence of asexual forms of *P. falciparum* in the peripheral blood smear.
2. The attending relative able and willing to give informed consent.
3. ≥2 years of age

*Exclusion Criteria*

1. Relatives unable or unwilling to give informed consent.
2. Patients who already have the features of aspiration pneumonia.
3. Pregnancy
4. Diabetic requiring insulin
5. Contraindications to enteral feeding:

-Circulatory shock

-Mechanical bowel obstruction / ileus / ischaemic colitis (redcurrant jelly stools)

-Severe diarrhea (> 6 per 24 hours), severe vomiting (> 6 per 24 hours) or severe dehydration due to either

-Pancreatitis (laboratory confirmed: serum amylase >500 U/L)

6. Known allergies to artesunate or quinine

7. Severely malnourished child (according to WHO criteria)

*Examination and Treatment*

On enrolment a full history and physical examination will be carried out. Nutritional status of the patient will be assessed by skin-fold thickness in the triceps region of the left arm and the mid upper arm circumference will be measured. Weight/height and presence of bilateral pedal edema (WHO criteria) for malnourished children will be assessed.

First line antimalarial treatment will be with intravenous artesunate, if available. Artesunate (Guilin No 2 Pharmaceutical Factory, Guangxi, Peoples’ Republic of China) will be given in a dose of 2.4 mg/kg body weight on admission, then at 12 hours, 24 hours, and thereafter once daily until oral medication can be taken reliably. Each 60 mg vial contains anhydrous artesunic acid which is dissolved initially in 1 ml 5% sodium bicarbonate and then mixed with 4 ml of 5% dextrose before injecting as a bolus into an indwelling intravenous cannula. When the patient has recovered sufficiently to take tablets, a full adult course of artemether-lumefantrine (CoartemR) will be given: 4 tablets twice daily for 3 days. Currently injectable artesunate is not registered yet in Bangladesh for the treatment of severe malaria. In case artesunate for injection is not available, the patient will be treated with i.v. quinine. A loading dose of 20 mg/kg will be given over 4 hours time followed by a dose of 10 mg/kg over 2 to 4 hours every 8 hours for a total of 7 days, or until the patient has recovered sufficiently to take tablets, in which case a full course of coartem will be given (see above). Patients will be managed in accordance with the World Health Organization guidelines 2006.

*Treatment allocation*

All patients will receive a NG tube. Patients will be randomized to either receive enteral feeding upon admission through the NG tube *(arm 1)*, or no feeding until able to take oral food or maximum until 60 hours (adults i.e. >12 years old) or 36 hours (children i.e. <12 years old) after admission followed by enteral feeding *(arm 2)*. The feed used in the study will be Revit-R/Renovit(patient with renal insufficiency) (Fasska SA, Louvain la Neuve, Belgium. The preparation comes as a powder, which will be dissolve in bottled water according to the instructions of the manufacturer (220g per liter water which will provide 1 kcal/ml) The feeding protocol is as follows:

Check position of NG tube before start of the first feed with a large syringe and before subsequent feeds by checking the position of a mark drawn on the tube at the time of insertion. Position the patient in the head tilt position (head 15° above horizontal). Start NG feeding with 2-4 ml/kg feeding every 2 hours in adult 10 feeds per day; omitting 2 late night feeds, this will deliver1000-2000kCal per 24 hours for adults weighing 50 kg. For children, the volume of enteral feeding will be calculated from the total amount of fluids to be given per 24 hours as follows: for age 2-4years: 100 - 120ml/kg/day; 4-8yrs 90-100ml/kg/day; 8-12yrs 70-90 ≥12 60-70ml/kg/day. The enteral feeding volume is derived from this total volume subtracting the volume given as i.v. The total amount of enteral feeding in children is divided in 12 feeds, given every 2 hours round-the-clock

Gastric retention will be measured just before the next feeding. Gastric retention is defined as> 4 ml/kg in adult and >2/3rd of the 2 hours previous feed in children. If gastric retention is present: feeding is discontinued and prokinetic drugs domperidon suppositories are added for adults domperidon 20 mg suppositories, every 8 hours; for children: domperidone suppository 15mg 1/2 suppository up to 5 years & 1 suppository beyond 5 years. In adults retention is reassessed 4 hourly. If the retained volume is <4 ml/kg, discard this volume, and feeds are continued every 2 hours as before. In children retention reassessed 2hourly and if the retention is < 2/3rd of the previous 2 hours feed this volume discard it, and feeds are continued every 2 hours as before.

Adult patients in the control arm (delayed start of enteral feeding) will receive 50-60ml 5% DS (glucose-saline)/kg/24 hours. The energy contents the infusion fluid containing 50-60g dextrose per liter around 200 kCal per liter, so that the energy given is 10-12 kCal/kg/ 24 hours, or 500-600 kCal for the average 50 kg patient. Paediatric patients in the control arm (arm 2) will receive 10% Dextrose in half strength saline (10% dextrose in 0.45% NaCl) in the volumes as above. This contains 400kCal/L, so that daily total calories delivered to the children not receiving enteral feeding will be for 2-4 y/o: 40-48 kCal/kg, for 4-8 y/o: 36-40 kCal/kg and for 8-12 y/o: 24-28 kCal/kg.

Family members will be instructed in the techniques for checking NG tube position using a pre-drawn mark, checking for gastric retention and giving NG feeds.

*General care measures for the patient with cerebral malaria will include:*

Head tilt position (15 to 30). Recording of GCS, blood pressure, respiratory rate, temperature, and oxygen saturation (pulse-oxymetry) every **4 hours.** Maintenance of an open airway, if needed, with a Guedel. Nursing on the side with turning every **2 hours** by the patient’s relatives to prevent bed sores. Catheterization of the bladder (Foley catheter) and recording of fluid input/output. Eye care with moisturizing eye ointment in the case of open eyes. Anti-pyretics: in case of fever, paracetamol 1g for adults and 15 mg/kg for children under 12 years will be given unless contra-indicated (liver failure). Once conscious and taking oral feed patients should be followed-up once daily.

*Investigations*

On admission a 10 ml blood sample will be taken for parasitaemia, complete blood count (CBC), including leukocyte differentiation and percentage of band form neutrophils, venous pH*, bicarbonate* and blood standardized base excess*, glucose*, electrolytes*, blood urea nitrogen*. (Parameters marked with * will be measured by i-STAT, using the EC8+ cartridges).

Peripheral blood parasitaemia and staging in thin film will be assessed on admission, followed by 12 hourly sampling until complete parasite clearance, defined by 2 consecutive negative peripheral blood slides.

Blood glucose will be checked 4 hourly until the patient regains consciousness. A blood glucose level below ≤2.8 mmol/l (50mg/dl) will be treated with 10% intravenous glucose (4 ml/kg body weight).

Blood count (i.e. total and differential white cell count, platelet count, haemoglobin and haematocrit), biochemistry and blood cultures will be repeated on indication. In particular, a blood count will be repeated when aspiration pneumonia or sepsis is suspected.

*Aspiration pneumonia*

Aspiration pneumonia will be diagnosed clinically from history and chest examination (fever, respiratory distress, auscultatory crackles, oxygen saturation), and confirmed by chest X-ray (CXR). All patients will have a CXR upon admission. If possible, a CXR will be done in the radiology department of CMCH. If the patient is not transportable, a bed side CXR will be performed. The CXR will be repeated upon indication and 3 days after the first one for follow-up. Treatment will be with antibiotics (intravenous ceftriaxone in combination with metronidazole). Oxygen will be given by nasal cannula or face mask where indicated. In the case of severe respiratory insufficiency, a concerted effort will be made to transfer the patient to the intensive care unit of CMCH for mechanical ventilation.

Analysis

*Primary outcome measures include:*

1. Incidence of aspiration pneumonia.
2. Incidence of hypoglycaemia (<2.2 mmol/L).
3. Coma recovery time. The coma recovery time is defined as the time till a Glasgow Coma Score of 15/15 (BCS 5/5 in preverbal children).

*Secondary outcome measures include:*

1. Incidence of sepsis.

Sepsis is defined as the presence of infection (other than malaria) in combination with systemic inflammatory response syndrome (SIRS) as indicated by ≥ 3 of the following criteria: prolonged fever i.e. axillary temperature  38ºC or core temperature of  36ºC; a heart rate of  90 beats/min; a respiratory rate of  20 breaths/min (up to 5yrs 40) or the use of mechanical ventilation for an acute respiratory process; a white-cell count of  12 x 109/l or  4 x 109/l, or a differential count showing > 10% immature neutrophils.

2. Time to sit independently, which will be assessed daily.

3. Time to speak independently, which will be assessed daily.

4. Time to eat independently, which will be assessed daily.

5. Total duration (days) of admission in the hospital.

6. Survival. In hospital mortality will be recorded.

Sample size calculation

To detect an increase in incidence in aspiration pneumonia from 10% to 30%, a sample size of 124 (62 in each treatment group) is required. After this pilot study the data will be analysed. If early enteral feeding appears to be promising regarding a decrease in hypoglycaemia or a shortening of coma recovery times, not at the expense of a significant increase in aspiration pneumonia, a larger follow-up trial will be planned.

Randomisation

Randomisation will be balanced in blocks of 20 by computerized method using STATA statistical software package.

Safety

Current practice in CMCH is to start on the day of admission with enteral feeding. However, if the current study shows a significant increase in the incidence of aspiration pneumonia in the group receiving early enteral feeding, randomization will be stopped, and patients will only receive enteral feeding after regaining consciousness, or 60 hours after admission. Since aspiration pneumonia is an identified risk, interim analyses will be performed after every 50 patients included. Interim data will be analysed by the Data Safety Monitoring Committee.

Benefits of the study

There is currently equipoise about the benefit of the start of early enteral feeding in patients with cerebral malaria in the tropical setting. Theoretical advantages (prevention of hypoglycaemia, restoration of immune function, etc) are countered by the increased risk of aspiration pneumonia. The study has a clear practical goal to guide this important part of the treatment of patients with cerebral malaria.

Finance

Costs involved in the study will be financed by the Wellcome Trust of Great Britain

References

1. SEAQUAMAT study group. Artesunate versus quinine for treatment of severe falciparum malaria: a randomised trial. Lancet 2005; 366: 717-725 [↑](#endnote-ref-2)

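### Entry does not require coma to persist after treatment of admission hypoglycaemia, and hypoglycaemia already present at admission is not set aside, so two of the three primary outcomes may be diluted

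*Protocol*

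**What the plan says.** All references are to the Protocol.

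- **Inclusion Criteria:** "Cerebral falciparum malaria defined as a GCS<11or BCS <3 (for pre-verbal children), and the presence of asexual forms of" *P. falciparum* in the blood smear. The section Place and Period of Study gives the same definition. Neither place asks for the score to be confirmed later.
- **Exclusion Criteria:** admission hypoglycaemia is not listed. The nearest item is "Diabetic requiring insulin". For another primary outcome, the condition at entry is excluded: "Patients who already have the features of aspiration pneumonia".
- **Investigations:** the admission blood sample includes "blood standardized base excess*, glucose*, electrolytes". After that, "Blood glucose will be checked 4 hourly until the patient regains consciousness". A low value (2.8 mmol/l or less) "will be treated with 10% intravenous glucose (4 ml/kg body weight"). None of these steps is linked to eligibility or to a repeat coma score.
- **Analysis:** the second primary outcome is "Incidence of hypoglycaemia (<2.2 mmol/L"). The third is the time to a GCS of 15, or a BCS of 5 in preverbal children. Neither has a stated starting point.
- **Opening background section:** "hypoglycaemia is a common complication, especially in patients receiving quinine". No rate is given, at admission or later.
- **Sample size calculation:** a larger follow-up trial will be planned if early feeding looks promising on hypoglycaemia or coma recovery without a significant increase in aspiration pneumonia.

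**The concern.** The trial asks whether early tube feeding shortens malarial coma and prevents hypoglycaemia. Low glucose can itself depress the coma score. A patient who is parasitaemic and scores below 11 because of low glucose meets the definition and may wake after the intravenous glucose, which both arms receive under the same rule. That recovery time carries little or no information about feeding. An admission value below 2.2 mmol/L also precedes any feed, yet the wording of the outcome does not set it aside.

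Such patients would add similar outcomes to both arms and shrink both contrasts. The decision on a follow-up trial depends on these two outcomes, so the risk is that a useful effect goes unseen.

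**Working it through.** **1. The plan's own figure.** For aspiration pneumonia at 10% v 30%, with 1:1 allocation, and assuming a two-sided 5% level, 80% power and pooled variance (the protocol states neither level nor power):

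n per arm = [1.96·√(2·0.2·0.8) + 0.8416·√(0.1·0.9 + 0.3·0.7)]² / 0.2² = (1.109 + 0.461)² / 0.04 = 61.6, rounded up to 62, or 124 in total.

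The stated 124 is reproduced. It rests on aspiration pneumonia alone, and this point does not alter it.

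**2. Does any section close the gap?** Inclusion Criteria sets a single score. Exclusion Criteria does not mention low glucose. Investigations treats low glucose without a return to the score. Examination and Treatment says that patients are managed under the WHO 2006 guidelines, but that sentence governs care and does not change the written entry criterion. The gap stays open.

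**3. Hypoglycaemia outcome, conditional on admission values being counted.** Let a be the share of patients below the outcome threshold at admission, equal in both arms, and p the risk of a new event. The observed proportion is a + (1 − a)·p. Assumptions, none from the protocol: a of 5–20%, and p of 20% with late and 10% with early feeding. Power is for 62 per arm (two-sided 5%, pooled z-test).

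| a | Late | Early | Difference | Ratio | Power |
|---|---|---|---|---|---|
| 0 | 20% | 10% | 10 points | 0.50 | 34% |
| 5% | 24% | 14.5% | 9.5 points | 0.60 | 27% |
| 10% | 28% | 19% | 9 points | 0.68 | 22% |
| 20% | 36% | 28% | 8 points | 0.78 | 16% |

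For example, at a = 10%: 0.10 + 0.90 × 0.20 = 0.28 and 0.10 + 0.90 × 0.10 = 0.19.

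With a larger assumed effect of 30% v 10%, power is 80% undiluted, then 70%, 61% and 46% at a = 5%, 10% and 20%. If admission values are not counted, none of this dilution arises.

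**4. Coma recovery.** Let f be the share whose recovery is set by the glucose, with no feeding effect. The average standardised effect shrinks by the factor (1 − f), and the number needed grows by 1/(1 − f)². Assume a true effect of 0.5 SD and an unchanged SD.

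| f | Effect (SD) | Power at 62 per arm | Inflation of n |
|---|---|---|---|
| 0 | 0.500 | 80% | 1.00 |
| 5% | 0.475 | 75% | 1.11 |
| 10% | 0.450 | 71% | 1.23 |
| 20% | 0.400 | 60% | 1.56 |

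The share f cannot be read off a. Hypoglycaemia may accompany a coma that is malarial, and treatment starts at 2.8 mmol/l while the outcome is set at 2.2 mmol/L, so the two groups differ.

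**The case against.** The other side has good arguments.

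- **Incidence ordinarily means new events.** The admission sample is also described apart from the 4-hourly checks, and a counting window is something an analysis plan commonly sets. This stands: the table in step 3 is conditional. It does not reach the entry criterion, because an analysis plan cannot undo an enrolment and has no required post-treatment score by which to identify these patients.
- **The background sentence does not establish hypoglycaemia at admission.** It points partly to quinine, hence to events during treatment, which the trial hopes to prevent. This stands: the size is unknown and could be small.
- **The loss looks larger as a ratio than as a difference.** At 20% v 10% the difference falls only from 10 points to 9.5–8, and power is already just 34% without dilution. The trial calls itself a pilot and is sized on another outcome. This stands and limits the weight of the point.
- **Entry at the time of the feeding decision suits a practical question in consecutive patients.** This is fair, but the re-score delays only patients who are being treated for low glucose.

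A reader might infer more than the documents support:

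- **That the contrast is biased.** Admission status precedes randomisation and is balanced in expectation.
- **That feeding cannot affect these patients.** It cannot prevent the admission episode, but it could affect a later one.
- **That entry rests on the coma score alone.** Parasites on the smear are also required; the score is the only coma condition.

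**Conclusion.** The point holds as a gap in the entry definition, with a smaller gap in the wording of the hypoglycaemia outcome. As written, a patient whose coma is wholly or partly due to low glucose can be randomised, and the recovery time may then reflect the glucose rather than the arm. The consequence is dilution of two of the three primary outcomes and some chance imbalance at 62 per arm.

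Its size cannot be taken from the protocol, which gives no admission rate, no hypoglycaemia rate by arm and no spread for coma recovery. All figures in steps 3 and 4 of the working rest on assumed values, and those in step 3 also on the reading that admission values count. The sample size of 124 is not disputed. The change is worth making because it is cheap and because the coma part cannot be repaired after enrolment.

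**What to change.** 1. In Inclusion Criteria, require the qualifying score (GCS below 11, or BCS below 3) to be confirmed on a re-score made after any admission hypoglycaemia has been treated under the existing rule, and before randomisation.
2. In Analysis, state that the primary outcome counts only hypoglycaemia first found on samples taken after randomisation and after that treatment. A new later episode in a patient who was low at admission still counts.
3. Record admission glucose as a baseline value.

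No dose or treatment threshold changes, and 124 stays as it is. The cost is one extra coma score in patients already under treatment (scores are taken every 4 hours anyway), a short delay to randomisation for them, and a few patients lost to eligibility. If those patients are replaced, recruitment takes slightly longer. If they are not, power for an assumed 0.5 SD effect on coma recovery is 77%, 75% and 70% at shares of 5%, 10% and 20%, which is still above the diluted 75%, 71% and 60%. Power for aspiration pneumonia would then also fall, so replacing them is preferable.

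### The rule after a safety stop drops the 36-hour feeding limit for children, and the only oral antimalarial course printed is the adult one

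*Protocol*

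**What the plan says.** **Who is enrolled.** The Inclusion Criteria admit patients "≥2 years of age", and the paediatric ward is one of the recruiting wards.

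**Delay in arm 2.** Treatment allocation withholds enteral feeding until the patient can eat, with a ceiling of 60 hours for adults (defined as over 12 years) and 36 hours for children (under 12 years).

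**After a safety stop.** The Safety section says that if early feeding significantly increases aspiration pneumonia, randomisation ends and "patients will only receive enteral feeding after regaining consciousness, or 60 hours after admission". The trigger is reviewed during the trial: "interim analyses will be performed after every 50 patients included".

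**Oral follow-on treatment.** Examination and Treatment addresses the patient who has recovered enough to swallow tablets, with no age or weight condition: "a full adult course of artemether-lumefantrine (CoartemR) will be given: 4 tablets twice daily for 3 days". For the quinine route the text is "in which case a full course of coartem will be given (see above". The same paragraph closes with "Patients will be managed in accordance with the World Health Organization guidelines 2006".

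**Control-arm energy.** The feeding text under Treatment allocation orders 70-90 ml/kg/day for ages 8-12, gives the paediatric control fluid as 400 kcal per litre, and prints 24-28 kcal/kg for that age band.

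**The concern.** The two main items are instructions that ward staff would follow for children. After a safety stop the Safety section becomes the operative feeding rule, and it carries no child limit. The authors chose a shorter ceiling for children in the allocation section, and nothing in the Safety section says they meant to lengthen it.

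For the oral course, a clinician looking for a child's dose finds one tablet count, labelled adult, and a cross-reference from the quinine route back to it. Elsewhere the protocol usually makes its doses usable for children. Artesunate, quinine and intravenous glucose are given per kilogram. Antipyretic dosing is split by age: "paracetamol 1g for adults and 15 mg/kg for children under 12 years". The prokinetic has its own child amounts: "for children: domperidone suppository 15mg 1/2 suppository up to 5 years & 1 suppository beyond 5 years".

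The energy figure and the age-12 gap are matters of accuracy and consistency.

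**Working it through.** **1. Feeding delay, the two sections side by side**

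| | Treatment allocation (arm 2) | Safety (after a stop) |
|---|---|---|
| Feeding may start earlier when | patient can eat | patient regains consciousness |
| Ceiling, adults | 60 h | 60 h |
| Ceiling, children | 36 h | 60 h (no separate limit) |

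Take a child who is still unconscious at 36 hours. Under the allocation section, enteral feeding starts then. Under the Safety section it starts on waking or at 60 hours, whichever comes first. The largest difference is 60 − 36 = 24 hours. For a child who wakes before 36 hours, the Safety rule adds no delay.

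**2. Oral course**

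The printed count is 4 tablets × 2 per day × 3 days = 24 tablets. It is the only count in the document, and no child schedule is given against which to compare it.

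**3. Control-arm energy**

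Inputs are the ordered volumes by age and 400 kcal/L = 0.4 kcal/ml, both from the feeding text. Energy (kcal/kg/day) = volume (ml/kg/day) × 0.4.

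| Age | Volume (ml/kg/day) | Computed (kcal/kg/day) | Printed (kcal/kg) |
|---|---|---|---|
| 2-4 y | 100-120 | 40-48 | 40-48 |
| 4-8 y | 90-100 | 36-40 | 36-40 |
| 8-12 y | 70-90 | 28-36 | 24-28 |
| 12 y and over | 60-70 | 24-28 | none |

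The first two bands reproduce exactly, so the method is the authors' own. The figure printed for 8-12 years is what the oldest band's volume gives, which points to a row slip. The printed range is too low by 28 − 24 = 4 at the lower end (4/28 = 14%) and 36 − 28 = 8 at the upper end (8/36 = 22%).

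**4. Age 12**

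Adults are over 12 and children under 12, so a patient whose age is recorded as 12 falls in neither group and has no stated ceiling.

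**The case against.** **On the feeding delay.** The two sections govern different phases, randomised treatment and care after randomisation has ended, and the 60 hours may be shorthand for the delayed arm as a whole. The starting conditions also differ. A patient who is awake but not yet eating could be fed sooner under the Safety rule, so a reader would be wrong to infer that it lengthens the wait for every child. These points narrow the problem to children unconscious beyond 36 hours. They do not remove it, because the Safety text states no child limit.

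**On the tablets.** The strongest objection is that the sentence calls the course adult, that the quinine sentence omits that word, and that the paragraph ends by invoking WHO guidelines that may well cover child dosing. This is also background treatment, and the protocol leaves other background drugs to usual practice: ceftriaxone and metronidazole have no printed dose for anyone. A reader might infer that the protocol prescribes adult doses to 2-year-olds, or that it contradicts itself. The documents do not support either reading. What stands is that a child dose is missing where an explicit adult count is addressed to the patient without restriction.

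**On the energy figure.** It is descriptive. Staff order volumes, and the volumes are as intended.

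**On age 12.** If age is treated as continuous, the adult group takes in almost everyone past the 12th birthday and the gap nearly closes.

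**Conclusion.** The Safety rule is wrong as written: it omits the 36-hour maximum that the protocol sets for children. The consequence is up to 24 hours of extra delay in enteral feeding, only for a child still unconscious at 36 hours, and only once a safety stop has occurred. A reader might go on to estimate how many patients this would affect. The protocol gives neither the number of children nor whether enrolment continues after a stop, so no such count can be derived. Nor does the delay mean a child without energy, provided the dextrose infusion specified for the delayed arm is also given after a stop; the Safety section does not say.

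The oral course is an unclear or omitted child dose. No overdose multiple can be stated from this document.

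The 8-12 year energy figure is a numerical error of 4-8 kcal/kg/day with no effect on any order. The unassigned age of exactly 12 is worth noting and no more.

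Severity is minor overall. None of these items enters the sample size calculation or changes the randomised comparison.

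**What to change.** - **Safety:** give the ceiling after a stop as 60 hours for adults and 36 hours for children.
- **Examination and Treatment:** limit the 4-tablet sentence to adults, and state weight-based artemether-lumefantrine dosing for children under the WHO guideline already invoked. Make it apply to both the artesunate and the quinine route.
- **Feeding text:** print 28-36 kcal/kg/day for ages 8-12.
- **Age 12:** assign patients of exactly 12 to one group. Which group is a clinical choice for the investigators, since it decides between a 36-hour and a 60-hour ceiling.

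The cost is two short safety edits, one corrected figure and one age decision. The arms, sample size, data collected and analysis do not change.

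### Sepsis needs 3 of 4 SIRS items but only two are charted routinely after admission, so it will be under-counted and depend on suspicion by staff who see the feeding

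*Protocol*

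**What the plan says.** In the Analysis section, incidence of sepsis is the first secondary outcome. It combines an infection that is not malaria with SIRS, the latter "as indicated by ≥ 3 of the following criteria". Four criteria follow: temperature; heart rate; respiratory rate, with the alternative "or the use of mechanical ventilation for an acute respiratory process"; and white cells (total count or immature forms). The respiratory item carries a separate figure for children up to 5 years. The heart-rate item has a single figure, 90 beats/min, for all ages.

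What is to be measured stands elsewhere. The general care measures call for "Recording of GCS, blood pressure, respiratory rate, temperature, and oxygen saturation (pulse-oxymetry) every" 4 hours. The Investigations section puts a full blood count with differential and band forms in the admission sample. After that: "Blood count (i.e. total and differential white cell count, platelet count, haemoglobin and haematocrit), biochemistry and blood cultures will be repeated on indication", and "In particular, a blood count will be repeated when aspiration pneumonia or sepsis is suspected". The admission list contains no blood culture. The Aspiration pneumonia section adds a chest X-ray for everyone on admission and a follow-up film 3 days later.

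**The concern.** The outcome definition and the measurement schedule do not match. One of the four SIRS items, heart rate, is not named among the observations to be recorded. Another, white cells, is measured after admission only if someone has already thought of infection. The third item needed to reach the threshold therefore depends on clinical suspicion.

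That matters because no blinding is described and the arms look different at the bedside: one receives tube feeds every 2 hours, the other intravenous glucose fluid. Suspicion, and with it the blood count, may differ between arms for reasons other than true sepsis.

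There is also an overlap. Aspiration pneumonia is an infection other than malaria, so a case that meets SIRS counts under both the primary harm outcome and sepsis. The protocol's introduction justifies early feeding partly by protection of the gut barrier and less bacteraemia. Sepsis is the listed outcome closest to that benefit, yet it mixes the hoped-for benefit with the feared harm.

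**Working it through.** **Inputs.** Threshold: at least 3 of 4 items (Analysis, secondary outcomes). Items on the 4-hourly record: temperature and respiratory rate (general care measures). Heart rate: on no schedule. White cells: on admission, then on indication (Investigations). The protocol gives no expected sepsis rate. Its one computed figure, 62 per group for aspiration pneumonia, does not enter this check.

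**Step 1: combinations that satisfy SIRS.** Exactly three positive: C(4,3) = 4. All four positive: C(4,4) = 1. Total 4 + 1 = 5.

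**Step 2: combinations that the recorded data can show.** At least three of the *measured* items must be positive. With two items measured that is impossible. With three measured, all three must be positive and the unmeasured one may be either, which gives 2 combinations.

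| Data available after admission | Items measured | Combinations shown |
|---|---|---|
| Scheduled record only (temperature, respiratory rate) | 2 of 4 | 0 of 5 |
| Scheduled record + count ordered on suspicion | 3 of 4 | 2 of 5 |
| Scheduled record + heart rate, no count | 3 of 4 | 2 of 5 |
| Scheduled record + heart rate + count | 4 of 4 | 5 of 5 |

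With a count but no heart rate, the 5 − 2 = 3 missed combinations are those where heart rate supplies the third positive item: with temperature and respiratory rate, with temperature and white cells, or with respiratory rate and white cells. The five combinations need not be equally common, so 2 of 5 is not an estimate that 40% of cases are found.

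**Step 3: possible escapes.** Mechanical ventilation is an alternative within the respiratory item and adds no further item. The admission count precedes any effect of feeding, so carrying it forward would not show sepsis arising afterwards.

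**Step 4: overlap with aspiration pneumonia.** Let *f* be the share of aspiration cases that meet SIRS and have no other source of sepsis, taken as equal in both arms. At the sample-size rates of 10% and 30%, the overlap contributes *f* × (30 − 10) = 20*f* percentage points to the difference in sepsis between arms: 0 at *f* = 0, 10 at *f* = 0.5, 20 at *f* = 1. The protocol gives no value for *f*, and 10% v 30% is the difference to be detected, not an expected result. This is a range under assumptions and estimates nothing.

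**The case against.** The strongest reply is that sepsis is found by clinical work-up, and the protocol provides for it: when aspiration pneumonia or sepsis is suspected a count is taken, and temperature, respiratory rate and white cells then make three. This stands. A reader might infer from the schedule that sepsis cannot be established in this trial at all; the documents do not support that. What remains is that all three measured items must then be positive, and that reaching them depends on suspicion.

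Second, the 4-hourly list describes nursing care and may not be the full data record. A pulse oximeter is in use at that round, and heart rate may well be noted. That is possible, but only oxygen saturation is named from it, and no later analysis plan can recover values that were not recorded.

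Third, a reader might infer that most recorded sepsis will be aspiration pneumonia counted again, enough to hide or reverse a benefit. For example, with other sepsis assumed to fall from 20% to 10% and *f* = 1, early feeding would show 10 + 30 = 40% against 20 + 10 = 30%. Those sepsis rates and *f* are assumed. Suspected sepsis is a separate trigger for the count, the triggers are introduced as examples, and the 3-day film does not wait for suspicion. The overlap is real, but its size is unknown.

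Fourth, little hangs on sepsis. The decision on a larger trial uses hypoglycaemia, coma recovery and aspiration pneumonia, and the stopping rule uses aspiration pneumonia. This is correct and limits the weight of the point. Fifth, charting heart rate does not make the detection of infection independent of suspicion. This is also correct.

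**Conclusion.** The point holds in a limited form. Routine data after admission cover 2 of the 4 SIRS items against 3 required. With a count ordered on suspicion, 2 of the 5 qualifying combinations can be shown and 3 cannot. Followed as written, the protocol will under-count sepsis, and ascertainment will depend on suspicion by staff who can see the feeding arm. The direction of any difference between arms cannot be derived from the documents. Sepsis also partly overlaps the primary harm outcome, to an unknown extent.

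This assumes that heart rate is not recorded elsewhere as trial data and that later counts are taken only on indication, as the text reads. It does not depend on the comparison signs in the SIRS cut-offs, which are not legible in the text available. It concerns a secondary outcome of a study that calls itself a pilot: it should be corrected, but it does not threaten the primary comparison.

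**What to change.** 1. Name heart rate in the 4-hourly record, in both arms. The oximeter already used at that round can supply it.
2. Derive SIRS from the charted values by one fixed rule, the same in both arms, including the time window within which the three items must occur.
3. Reconcile the definition for children: respiratory rate has a separate figure for the youngest, heart rate has none, and enrolment starts at 2 years. Until that is settled, charted heart rate may be uninformative in young children.
4. Report sepsis in two parts: aspiration pneumonia as the only source, and any other source. Use the second part for the gut-barrier and bacteraemia question.
5. Reconcile the statement that blood cultures are repeated with the admission list, which contains none.

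The cost is one more number at an existing round and one more row in the results. The non-aspiration part will have fewer events and less precision. Combinations that need white cells will still require a count ordered on indication, and detection of infection will still depend partly on clinical suspicion; the report should say so.
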